#### Sample size

The underlying study hypothesis is that the percentage of subjects achieving daytime blood pressure normalization will be 25% larger in the HBPT group. Using a two-tailed test with a 0.05 significance level and an 80% power, the estimated number of patients to be randomized is 252 (including a 25% drop-out rate), with 84 patients randomized to CM and 168 to HBPT.

#### Planned statistical analyses

Analysis will be performed on patients valid for intention-to-treat, defined as all subjects with at least one visit during the randomized phase of the study and with valid ambulatory blood pressure recordings at baseline, after 24 and 48 weeks of follow-up even in the presence of protocol violations. A confirmatory analysis on the per-protocol (patients who have successfully completed the study without major protocol violations) is also foreseen.

The demographic and clinical characteristics of the two study groups will be compared at baseline by analysis of variance (continuous variables) or by Mantel-Haenszel Chi-square test (categorical variables), in order to verify the between-group homogeneity at randomization. The same tests will be used to compare primary and secondary study endpoints between the CM and HBPT groups. If deemed necessary, in addition to the univariate approaches, multivariate analysis methods will be used.

The type and frequency of drug-related adverse events will be reported for each randomization group. The absolute rate of adverse events will be compared between groups using the Chi-square test.

The minimum level of statistical significance will be set at *P* <0.05.

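### The set labelled intention-to-treat requires valid ambulatory recordings at baseline, week 24 and week 48, so both primary endpoints are analysed in completers only

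*Protocol article*

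**What the plan says.** All references are to the protocol article.

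- **Planned statistical analyses, first condition:** "Analysis will be performed on patients valid for intention-to-treat, defined as all subjects with at least one visit during the randomized phase".
- **Same sentence, second condition, joined by *and*:** "with valid ambulatory blood pressure recordings at baseline, after 24 and 48 weeks of follow-up even in the presence of protocol violations".
- **Same section, per-protocol set, offered as the confirmatory analysis:** "patients who have successfully completed the study without major protocol violations".
- **Primary outcome measures:** daytime normalisation at week 24 (Visit 5) and at week 48 (Visit 7) are listed as two separate primary endpoints.
- **Ambulatory blood pressure monitoring:** recordings are made at Visits 1, 5 and 7 only, and Visit 7 is the final visit.
- **Sample size:** "the estimated number of patients to be randomized is 252 (including a 25% drop-out rate"), "with 84 patients randomized to CM and 168 to HBPT".

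The article names no other population for the primary endpoints.

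**The concern.** Intention-to-treat compares patients as randomised. Here, membership depends on two events after randomisation: a valid recording at week 24 and another at week 48. The clause about protocol violations keeps violators in the set, but it does not bring back anyone without a recording.

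Three things follow.

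1. Anyone who leaves before week 48 is out of both primary analyses, although the result will be reported as intention-to-treat.
2. The week-24 endpoint loses patients whose outcome at week 24 is known, because of something that happens up to 24 weeks later.
3. Both planned analyses leave out the drop-outs, so agreement between them says nothing about drop-out bias.

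The design makes informative loss plausible. The trial is open label. Telemonitored patients get feedback on a display, monthly reports to the investigator and possible drug changes between visits; control patients do not. Retention could therefore depend on arm and on blood pressure control. The Discussion itself links poor adherence to poor control.

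**Working it through.** **Inputs from the article:** 252 randomised (84 CM, 168 HBPT); 25% drop-out; two-sided 0.05.

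**1. The planned figure.** 252 × 0.75 = 189 evaluable (84 × 0.75 = 63 CM; 168 × 0.75 = 126 HBPT). In reverse, 189 / 0.75 = 252, so the drop-out step reproduces. The full calculation behind 252 cannot be reproduced uniquely, because the article gives no CM rate and does not say whether the 25% difference is absolute or relative. That is a separate matter.

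**2. Patients outside the set.** 252 − 189 = 63 (21 CM + 42 HBPT if loss is equal by arm), taking drop-out to mean no valid week-48 recording.

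**3. What the missing outcomes could do.** Assumed example: completers normalised 19/63 CM and 69/126 HBPT, a difference of 54.8% − 30.2% = 24.6 points. Over all 252:
- all missing CM normalised, no missing HBPT normalised: 69/168 − (19 + 21)/84 = −6.5 points;
- the reverse: (69 + 42)/168 − 19/84 = +43.5 points.

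**4. Illustration of bias with no true effect.** Assumed: 40% normalised in both arms if all were followed, and 25% loss in both. CM loss is unrelated to blood pressure. HBPT retains 90% of controlled and 65% of uncontrolled patients.
- HBPT retention: 0.4 × 0.90 + 0.6 × 0.65 = 0.36 + 0.39 = 0.75.
- HBPT completer rate: 0.36 / 0.75 = 48%; CM completer rate: 40%.
- Pooled two-proportion test, 63 v 126, exact enumeration: two-sided rejection rate 0.180, against a nominal 0.05.

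Equal drop-out rates therefore do not protect the comparison. With equal loss and equal prognosis among drop-outs, there is no bias.

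**5. Does counting missing as not normalised cure this?**
- Same scenario: CM 0.40 × 0.75 = 30%; HBPT 0.48 × 0.75 = 36%. With 84 v 168 the rejection rate is about 0.15, barely better than 0.18.
- Loss unrelated to blood pressure but unequal (CM 35%, HBPT 20%), 40% normalised in both: completers show 40% v 40% and reject at about 0.05. Missing-as-failure gives 0.40 × 0.65 = 26% v 0.40 × 0.80 = 32% and rejects at about 0.16.

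So it is useful as a sensitivity analysis but is not a neutral primary rule.

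**6. Power under missing-as-failure.** Assumed: 25 absolute points among completers and 25% missing per arm. The difference becomes 25 × 0.75 = 18.75 points. Normal approximation, pooled test:

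| CM completer rate | Completers, 63/126 | Missing as failure, 84/168 |
|---|---|---|
| 20% | 0.94 | 0.91 |
| 30% | 0.91 | 0.85 |
| 40% | 0.91 | 0.82 |
| 50% | 0.93 | 0.81 |

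If the 25% is relative, power at 84/168 is only about 10–30% over the same CM rates. It is also low in completers (about 11–38%), so the cause is the effect size and not the analysis set.

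**The case against.** **The sentence may mean a valid recording at the time point being analysed.** That reading is conceivable, but it is not what is written: the recordings are listed jointly as a condition for entering one set. It would restore the week-24 outcomes of later drop-outs, but would still exclude everyone lost by week 48.

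**Missing-data detail belongs in an analysis plan.** That would hold if the article left the population open. It fixes the population, and a plan that followed it would inherit the fault.

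**The bias is possible, not shown.** This stands. The 18% needs outcome-dependent loss in one arm only, with a 25-point gap in retention between controlled and uncontrolled patients, and nothing in the article supports those figures. A reader might infer that the trial will be biased in favour of telemonitoring; the documents do not support that.

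**Three other inferences go too far.**
- *The definition itself drops a quarter of patients.* The 25% is a planning allowance. Actual exclusions could be fewer, or more once invalid recordings count.
- *The per-protocol set is almost the same set.* Major violators are kept in one and removed from the other, and no violation rate is given, so the overlap is unknown. Only the shared restriction to completers is established.
- *Counting missing as failure solves the problem with no extra patients.* Step 5 shows that it can keep or create bias. The power assurance holds only if the 25% means absolute points.

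**Conclusion.** The point holds and should be corrected before analysis. The set named intention-to-treat is a completers' set, and it discards observed week-24 outcomes without need. Both primary endpoints are affected, and the per-protocol analysis cannot reveal drop-out bias.

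That conclusion rests on the wording and the recording schedule alone. The count of 63 of 252 rests on the planned 25% drop-out occurring and meaning no valid week-48 recording. The 18% false-positive rate is an illustration under assumed loss, not an estimate. The size and direction of any real bias are unknown.

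**What to change.** 1. Define intention-to-treat as all randomised patients, in their allocated arm.
2. Analyse week 24 and week 48 separately, with no week-48 condition on the week-24 endpoint.
3. In the primary analysis, handle missing ambulatory recordings by multiple imputation using arm, baseline ambulatory pressure, any week-24 ambulatory pressure, and the office pressure already measured at Visits 3 to 7.
4. As sensitivity analyses, add missing-as-not-normalised and other missing-not-at-random scenarios. Missing-as-not-normalised should not stand alone, because it is itself biased when loss differs by arm.
5. Relabel the present set as completers and keep it as supportive.

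The cost is a wording change, a little more analysis work and dependence on imputation assumptions. No new measurements are needed. Under the missing-as-not-normalised analysis, power at 84/168 is about 81–91%, but only if the planned difference is 25 absolute points and the CM completer rate lies between 20% and 50%. The article should state which reading of the 25% applies before that assurance is relied on.

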### Study procedures

Besides baseline screening and randomization visits (Visit 1 and 2), all the patients will be re-assessed at 4 weeks (Visit 3), 12 weeks (Visit 4), 24 weeks (Visit 5), 36 weeks (Visit 6), and 48 weeks (Visit 7) of follow-up. If the Investigator deems it appropriate extra visits can be planned. Figure 
3 presents an overview of variables measured at each time point of the study. All data collected during the study will be entered manually by the Investigator in a web-based electronic case report form (e-CRF) linked to the telemedicine system.

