Four weeks later (Visit 3) the patients will be visited again by the Investigator and the medical therapy will be adjusted on the basis of office blood pressure (target, <140/90 mmHg) in the CM group or home blood pressure (target, <135/85 mmHg) in the HBPT group. Office blood pressure will still be measured by the Investigator with the same automatic electronic instrument used for self-measurement, in all patients, including those randomized to HBPT. Additional visits are scheduled 12, 24, 36, and 48 weeks after randomization (Visits 4, 5, 6, and 7). During each of these visits office blood pressure will be measured and antihypertensive medication will be changed according to office (CM group) or home blood pressure values (HBPT group). Drug treatment can also be changed in the patients of the HBPT between the scheduled visits, based on the home blood pressure report monthly received and reviewed by the Investigator. The same laboratory tests performed at screening visit and a 24-h ambulatory blood pressure recording will be repeated at Visits 5 and 7. During these two visits psychological tests will also be administered, with the exclusion of STAY, TDP, TAP, and TCI test, administered only at Visit 2.

Occurrence of adverse events, adherence to therapy and concomitant therapies will be checked at all visits during the trial. Evaluation of adherence to drug treatment will be based on patient’s report on amount of prescribed drug intake and on counting the quantity of study medication taken by the patient, comparing this datum with the quantity expected to be returned. The Investigator will instruct each patient to bring back used and unused drug blisters at each visit. The compliance will be computed as the ratio between the number of pills taken and the number of pills which should have been taken, expressed as a percentage, and will then be graded as follows: excellent (100% of prescribed pills taken), good (80% to 99%), fair (40% to 79%), or poor (<40%).

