### Ambulatory blood pressure monitoring

At Visit 1, and subsequently at Visit 5 and at final visit (Visit 7) an ambulatory blood pressure monitoring will be performed non-invasively over 24 h by an oscillometric validated device
[36,37]. Current Guidelines will be followed for proper recording performance
[38,39]. The monitoring cuff will be wrapped around the non-dominant arm and the patient will be asked to keep her/his arm still during the automatic blood pressure measurements. The device will be programmed to measure blood pressure every 15 min during the whole 24 h. Each recording will start in the morning, before 07:00 and 10:00, immediately after office blood pressure assessment. Patients will then be sent home, asked to resume normal life, and to come back 24 h later for removal of the device.

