#### Secondary outcome measures

A series of psychological and clinical variables will be used as secondary endpoints.

Scoring of the different psychological questionnaires will be computed for the HBPT and CM groups and compared between groups. They will be used to quantify therapeutic adherence, and compared with evaluation of compliance based on the patient’s report.

The following clinical endpoints will also be evaluated: (1) the percentage of patients with office blood pressure normalization (<140/90 mmHg) after 24 and 48 weeks; (2) percentage of patients with home blood pressure normalization (average <135/85 mmHg) after 24 and 48 weeks in the HBPT group; (3) changes in average 24-h systolic and diastolic blood pressure after 24 and 48 weeks *vs*. baseline; (4) changes in office systolic and diastolic blood pressure after 24 and 48 weeks *vs*. baseline; (5) changes in average home systolic and diastolic blood pressure after 24 and 48 weeks *vs*. baseline in the HBPT group; (6) the number of antihypertensive drugs prescribed after 24 and 48 weeks *vs*. baseline; (7) the number of office or phone visits after 24 and 48 weeks *vs*. baseline; (8) direct costs of patient management, based on additional medical visits and laboratory tests performed between baseline and 24 and 48 weeks; (9) adherence to treatment, as reported by the patient (the assessment of adherence and persistence to therapy will also be done indirectly, by evaluating adherence to the home blood pressure monitoring program and by evaluation of the psychological tests); (10) difference in target organ damage score between baseline and week 24 and 48 of the study; (11) difference in cardiovascular risk level between baseline and week 24 and 48 of the study according to Heart Score (ESH-ESC) and Framingham algorithm
[40,41]; (12) difference in the rate of cardiovascular events between baseline and 24 and 48 weeks of follow-up; and (13) the number of subjects showing regression of metabolic syndrome after 24 and 48 weeks from the randomization.

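### As worded, the only main analysis set requires a valid week-48 ambulatory recording and makes no exception for cardiovascular events, so patients who die before that recording drop out of the event comparison

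*Protocol article*

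**What the plan says.** All references are to the protocol article.

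- **Main set.** Planned statistical analyses opens with a general statement of who is analysed: patients with at least one visit after randomisation and "with valid ambulatory blood pressure recordings at baseline, after 24 and 48 weeks of follow-up even in the presence of protocol violations". The set is called intention-to-treat. The sentence is not limited to the ambulatory blood pressure endpoints.
- **Comparisons.** The same section continues: "The same tests will be used to compare primary and secondary study endpoints between the CM and HBPT groups". It names no separate population for any secondary endpoint.
- **Other set.** The confirmatory per-protocol set consists of "patients who have successfully completed the study without major protocol violations".
- **Event endpoint.** Secondary outcome measures, item 12, is the "difference in the rate of cardiovascular events between baseline and 24 and 48 weeks of follow-up". Study objectives also lists the frequency of cardiovascular events among the outcomes.
- **Recording schedule.** "At Visit 1, and subsequently at Visit 5 and at final visit (Visit 7) an ambulatory blood pressure monitoring will be performed" (Ambulatory blood pressure monitoring). Visit 5 is week 24 and Visit 7 is week 48.
- **Adverse events.** "The type and frequency of drug-related adverse events will be reported for each randomization group". Their overall rate is compared by chi-square test, and no population is named for that comparison.

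**The concern.** For an ambulatory blood pressure endpoint, requiring a recording restricts the analysis to patients with data. For an event endpoint, the same requirement makes inclusion depend on the outcome: a fatal event before week 48 removes the patient who had it. The patient's earlier non-fatal events go as well.

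Three quantities are affected in different ways:

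- The count of events falls.
- The event rate falls only if patients with events are lost more often than patients without.
- The odds ratio between arms shifts only if that excess loss differs by arm. This is conceivable in an open-label trial where one arm has closer contact, but nothing in the document shows it.

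Study sites and population describes these patients as having raised short-term cardiovascular risk, so a count by arm that leaves out deaths would be an awkward result to report.

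**Working it through.** **Step 1: logic, with no assumed rates.** A patient who dies before Visit 7 has no week-48 recording, so the patient is not in the main set. The patient has not completed the study, so the patient is not in the per-protocol set either. The number of deaths before the week-48 recording is thus zero in both arms of either set. A patient who has an event and withdraws before Visit 7 is excluded in the same way. A patient who has a non-fatal event and attends Visits 5 and 7 with valid recordings stays in.

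**Step 2: inputs for an illustration.** From Sample size: 84 patients in conventional management (CM), 168 in home telemonitoring (HBPT), 25% drop-out. At that drop-out, 252 × 0.25 = 63 patients (21 CM, 42 HBPT) could lack the week-48 recording. The document gives no event risk, fatal share or loss by event status, so these are assumptions:

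- p = event risk, 4% in both arms (2% and 6% also tried)
- d = share of event-free patients lost, 0.25
- w = share of event patients lost

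Counted events = n·p·(1−w). Counted event-free patients = n·(1−p)·(1−d). Analysed odds ratio, HBPT to CM = true odds ratio × (1−w_H)/(1−w_C) × (1−d_C)/(1−d_H). The last factor is 1 when d is equal by arm.

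**Step 3: deaths only.** Let f be the share of event patients who die before the week-48 recording; the remainder are lost at 25%, so w = f + (1−f)·0.25. Events expected in all 252: 252 × 0.04 = 10.08. Event-free patients counted: 241.92 × 0.75 = 181.44.

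| f | w | Events counted | Analysed rate |
|---|---|---|---|
| 0 | 0.250 | 7.56 | 7.56/189.00 = 4.00% |
| 0.10 | 0.325 | 6.80 | 6.80/188.24 = 3.61% |
| 0.20 | 0.400 | 6.05 | 6.05/187.49 = 3.23% |
| 0.30 | 0.475 | 5.29 | 5.29/186.73 = 2.83% |

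Deaths therefore remove a further 7.56 − 6.80 = 0.76 to 7.56 − 5.29 = 2.27 events. With f equal by arm, the odds ratio stays at 1.00. With f = 0.30 in CM and 0.10 in HBPT it is 0.675/0.525 = 1.29; reversed, 0.78.

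**Step 4: differential loss for any reason.** This scenario does not isolate deaths. Take w = 0.50 in CM and 0.25 in HBPT, with p = 4%.

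- CM: 1.68/(1.68 + 60.48) = 2.70%
- HBPT: 5.04/(5.04 + 120.96) = 4.00%
- Odds ratio 0.75/0.50 = 1.50
- SE of the log odds ratio = √(1/1.68 + 1/60.48 + 1/5.04 + 1/120.96) = 0.905, approximate 95% interval 0.25 to 8.8

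Reversing the arms gives 0.67, and equal loss gives 1.00. At p = 2% or 6% the odds ratio is still 1.50, with 3.36 or 10.08 events counted.

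**Step 5: all randomised patients, as an upper limit.** At 4%: 3.36/84 against 6.72/168, odds ratio 1.00, SE 0.682, interval 0.26 to 3.8. These counts assume that every event is captured. Events after withdrawal would not be, so the real counts would be lower.

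**The case against.** **The set is not expressly assigned to item 12.** A reader might infer that the protocol states this population for every secondary endpoint. It does not: the sentence covering secondary endpoints speaks of tests, not populations. The article is also a condensed account, and a separate set for clinical events could sit in the full protocol or analysis plan. This stands as a limit on certainty. Even so, the population sentence is general, has no exception, and is followed only by a narrower set. The point concerns a stated rule, not a missing detail.

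**The week-24 loss depends on the reading.** If each recording is required only for its own time point, a patient with a valid week-24 recording who dies at week 30 stays in the week-24 comparison. The wording favours a joint requirement but does not settle it. The week-48 exclusion holds on either reading.

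**The consequence is small.** Fatal shares of 10% to 30% among 10.08 expected event patients mean about 1 to 3 deaths in 252 patients. The interval is wide before and after the change. This is correct, and no main conclusion of the trial would turn on it.

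**Adverse-event reporting partly covers the gap.** The overall adverse-event rate is compared between arms without a stated recording condition. That mitigates the problem. It does not replace item 12, because types are promised only for drug-related events. Since no population is named there, no error is claimed in that comparison.

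**The point follows from the wider definition.** The same completers' set under an intention-to-treat label also governs the primary endpoints. That is true, but the event endpoint needs its own remedy because it does not depend on a recording.

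**Conclusion.** The point holds as a statement about the wording. Deaths before the week-48 recording are excluded from the week-48 event comparison by construction, and from the week-24 comparison if the recordings are jointly required. Events in patients who withdraw before Visit 7 are lost as well.

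The size is known only under assumptions. At a 4% event risk and 25% other loss, deaths cut the counted events from 7.6 to between 6.8 and 5.3, and the analysed rate from 4.0% to between 3.6% and 2.8%.

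A reader might infer that the comparison is biased toward one arm. The document does not support that: the odds ratios of 1.29 or 0.78, and 1.50 or 0.67, come from assumed differences in loss between arms, and equal loss gives 1.00. A reader might also infer that every patient with an event is lost. That is not so either, since those who attend both visits with valid recordings stay in.

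The change is worth making, mainly for a fuller count of deaths and events by arm. It would not make the comparison precise.

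**What to change.** In Planned statistical analyses, state that item 12 is analysed in all randomised patients by assigned arm, counting every event recorded from randomisation to Visit 7 or last contact, with no ambulatory-recording requirement. List deaths and withdrawals by arm. Keep the recording condition for the ambulatory blood pressure endpoints only.

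No extra patients or visits are needed. Study procedures already provides for the collection: "Occurrence of adverse events, adherence to therapy and concomitant therapies will be checked at all visits during the trial", and study data are entered in an electronic case report form.

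The costs are modest:

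- Denominators will differ from those of the ambulatory endpoints.
- Follow-up is unequal for early leavers, so follow-up time by arm should stand beside the proportions. This assumes that event and visit dates are recorded.
- Events after withdrawal are still not recovered.

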### Randomization

Randomization will be performed using a blocked randomization procedure (computerized random numbers), in order to obtain equal numbers in each study arm. Patients will be randomized to CM or HBPT (1:2). In order to prevent selection bias, the allocation sequence will be concealed from the Investigator enrolling and assessing patients in sequentially numbered, opaque, and sealed envelopes.

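### Continuous secondary endpoints are compared by ordinary analysis of variance in 1:2 arms, which does not hold the 5% level if the arms' SDs differ materially (minor)

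*Protocol article*

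**What the plan says.** The Planned statistical analyses section of the protocol article names the baseline tests: "analysis of variance (continuous variables) or by Mantel-Haenszel Chi-square test (categorical variables". It then extends them: "The same tests will be used to compare primary and secondary study endpoints between the CM and HBPT groups". The only other method mentioned is optional and not specified: if judged necessary, "in addition to the univariate approaches, multivariate analysis methods will be used". Nothing is said about the variance assumption.

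The arms are unequal by design. Randomization states "Patients will be randomized to CM or HBPT (1:2", and Sample size repeats it: "with 84 patients randomized to CM and 168 to HBPT".

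The secondary endpoints include changes in 24-h and office blood pressure, questionnaire scores, the number of drugs, the number of office or phone visits, and "direct costs of patient management, based on additional medical visits and laboratory tests performed". Both primary endpoints are proportions with normal daytime pressure.

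**The concern.** Two-group analysis of variance in its usual form is the pooled-variance t-test. When the arms are the same size, pooling gives the right standard error even if the SDs differ. With 1:2 arms the larger arm dominates the pooled variance. The standard error is then too large if the larger arm is the more variable one, and too small if the smaller arm is.

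The design gives a reason to expect unequal spread in some endpoints. According to Study procedures and Home blood pressure monitoring, only HBPT patients have drug changes between visits, or extra visits, prompted by the home readings reports. These feed into visit counts and costs. If they make HBPT the more variable arm, the planned test is conservative and may miss a real difference in resource use, which the article presents as one of the questions the trial will address.

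**Working it through.** **Inputs.** Arm sizes 84 and 168, two-sided 0.05 and 80% power ("Using a two-tailed test with a 0.05 significance level and an 80% power") and drop-out ("including a 25% drop-out rate") come from Sample size. After drop-out, 84 × 0.75 = 63 and 168 × 0.75 = 126. The 80% is stated for the binary primary endpoint and serves here only as a reference level. The article gives no SDs, so the SD ratio is an assumption and a range is shown. It also states no figure on this point that could be reproduced.

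**Formulas.**
- Pooled variance: s_p² = ((n₁−1)s₁² + (n₂−1)s₂²)/(n₁+n₂−2).
- Standard error the test uses: √(s_p²(1/n₁+1/n₂)).
- True standard error: √(s₁²/n₁ + s₂²/n₂).
- With R = standard error used / true standard error, type I error ≈ 2·P(Z > 1.96R).
- Power of a comparison that would have 80% with the correct standard error ≈ Φ(1.96 + 0.842 − 1.96R).

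**Worked case: HBPT SD 1.5 times CM SD.** Set the CM SD to 1.
- s_p² = (62×1 + 125×2.25)/187 = 343.25/187 = 1.836.
- Standard error used = √(1.836 × (1/63+1/126)) = 0.209.
- True standard error = √(1/63 + 2.25/126) = 0.184.
- R = 1.138, so 1.96R = 2.231.
- Type I error ≈ 2.6%. Power ≈ Φ(2.802 − 2.231) = Φ(0.571) ≈ 72%.

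**Reverse case: CM SD 1.5 times HBPT SD.** Set the HBPT SD to 1.
- s_p² = (62×2.25 + 125×1)/187 = 264.5/187 = 1.414.
- Standard error used = 0.184; true = 0.209; R = 0.878.
- 1.96R = 1.722, so type I error ≈ 8.5%.

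**Range at 63/126, normal data.** The pooled and Welch columns are from simulation with 200,000 trials per row.

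| HBPT SD / CM SD | R | Pooled test | Welch test |
|---|---|---|---|
| 0.50 | 0.815 | 11.1% | 5.0% |
| 0.67 | 0.878 | 8.4% | 5.0% |
| 0.80 | 0.929 | 6.9% | 5.0% |
| 0.90 | 0.965 | 5.9% | 5.1% |
| 1.00 | 1.000 | 5.0% | 5.0% |
| 1.10 | 1.032 | 4.3% | 5.0% |
| 1.25 | 1.076 | 3.5% | 5.0% |
| 1.50 | 1.138 | 2.6% | 5.0% |
| 2.00 | 1.226 | 1.6% | 5.0% |

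The rows for 0.80, 0.67 and 0.50 correspond to a CM SD of 1.25, 1.5 and 2 times the HBPT SD. Results at 84/168 are nearly the same.

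**Is the allocation the cause?** Yes. With 63 per arm, the pooled test stays at 5.0% to 5.1% over the same SD ratios.

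**Skewed data.** Gamma-distributed, cost-type data with equal means at 63/126, 40,000 trials per row:

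| CV in CM | CV in HBPT | Pooled test | Welch test |
|---|---|---|---|
| 1.0 | 1.0 | 5.0% | 5.2% |
| 1.0 | 1.5 | 3.1% | 4.9% |
| 1.5 | 1.0 | 8.6% | 6.3% |
| 2.0 | 1.0 | 12.2% | 8.0% |

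Welch is closer to 5% wherever the spreads differ, but it is not exact when the smaller arm is the more skewed one.

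**The case against.** The article says analysis of variance without stating the variance assumption, and a Welch form could stand in an analysis plan that is not shown. It plans no confidence intervals. It does not assign visit counts, drug counts or costs to analysis of variance by name, and a drug count with few values could go to the Mantel-Haenszel test. Study procedures allows extra visits in either arm, which narrows the contrast. Spread in counts and costs usually rises with the mean, so equal means with a two-fold SD difference would be unusual.

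Most of this stands as a limit on the point. A reader might infer that false positives are the main danger. The documents do not support that: their only mechanism for unequal spread adds variability to HBPT, the larger arm, which makes the test conservative. A reader might also infer that reported intervals would be wrong, or that any difference in spread invalidates the P values. The first has no basis because no intervals are planned, and the second fails because ratios of 0.9 to 1.1 hardly matter.

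The objection does not remove the core. The article names a method rather than leaving it open, its ordinary meaning is the equal-variance test, and the optional multivariate methods do not address unequal variances.

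**Conclusion.** The point holds as a minor and conditional one. If analysis of variance is meant in its ordinary form and the SDs differ materially, the 5% level is not held for continuous secondary endpoints in 1:2 arms. For visits and costs the likelier consequence is lost power: 80% becomes about 72% if the HBPT SD is 1.5 times the CM SD. Inflation to between 6.9% and 11% needs CM to be the more variable arm by a factor of 1.25 to 2, and the article gives no ground for expecting that in visits or costs. All SD ratios are assumptions.

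The binary primary endpoints are not affected. Baseline comparisons use the same test, but randomization makes the SDs equal in expectation there, so nothing material follows for them.

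**What to change.** In Planned statistical analyses, for between-arm comparisons of continuous endpoints, replace ordinary analysis of variance with an unequal-variance method: a Welch test, or linear regression or ANCOVA with heteroscedasticity-robust standard errors. For skewed costs and visit counts, state that arm means will be compared by a robust or bootstrap method, because Welch alone is not exact there. How much a bootstrap would gain for these endpoints has not been computed here.

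The change affects wording only and needs no further patients, data or procedures. If the variances are in fact equal, the loss is about 0.3 points of power (73.3% against 73.0% in simulation).

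### With 84 v 168 patients and few cardiovascular events, the planned chi-square test can call 2 v 0 a significant benefit of HBPT; an exact test is needed for sparse secondary endpoints

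*Protocol article*

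**What the plan says.** Under Planned statistical analyses, baseline comparisons of categorical data use the "Mantel-Haenszel Chi-square test (categorical variables"), and the plan continues: "The same tests will be used to compare primary and secondary study endpoints between the CM and HBPT groups". The same section gives one threshold for all of this: "The minimum level of statistical significance will be set at" P<0.05. It mentions no exception for small counts, no exact alternative and no continuity correction. The further methods it allows if needed are multivariate ones.

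Under Secondary outcome measures, item 12 is the "difference in the rate of cardiovascular events between baseline and 24 and 48 weeks of follow-up". No expected event rate is given.

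The arms are unequal. Randomization says "Patients will be randomized to CM or HBPT (1:2"), and Sample size says "with 84 patients randomized to CM and 168 to HBPT", "including a 25% drop-out rate".

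**The concern.** A chi-square P value relies on a large-sample approximation. With 84 and 168 patients followed for 48 weeks, cardiovascular events may be few, and the expected count in CM may be well under 5. With unequal arms the approximation is then poor in a lopsided way. An event in the smaller arm moves the statistic much more than an event in the larger arm, and here the smaller arm is the control.

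At stake is a claim, on a clinically weighty secondary outcome, that HBPT significantly reduces cardiovascular events when the data are two chance events in CM and none in HBPT.

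**Working it through.** **Inputs.** From Sample size: CM 84, HBPT 168, total N = 252. From Planned statistical analyses: Mantel-Haenszel chi-square, P<0.05, read here as one unstratified 2×2 table without continuity correction. Item 12 is read as the number of patients with an event in each arm. Event risk: not in the protocol, so 0.5% to 3%, equal in both arms, is assumed, with 5% added as a check. The plan gives no figure of its own for this endpoint to reproduce.

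**Statistic.** With a events in CM, b in HBPT and m = a + b:

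- E = 84m/252 = m/3
- V = 84 × 168 × m × (252 − m) / (252² × 251)
- X² = (a − E)²/V, compared with 3.84

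If all m events fall in CM, this reduces to X² = 2m × 251/(252 − m). If all fall in HBPT, it is X² = m × 251/[2(252 − m)]. For the same m the first is four times the second; that factor comes from the 1:2 allocation.

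**Benefit side.** 2 v 0: X² = 4 × 251/250 = 4.016, P=0.045. The exact chance that both of two events fall in CM under no effect is (84 × 83)/(252 × 251) = 6972/63252 = 0.110, which is also the two-sided Fisher P. Twice that single tail is 0.220. The tables 3 v 0, 4 v 1 and 5 v 2 are also called significant (P=0.014, 0.026, 0.030), while their one-sided exact tails are 3.6%, 4.4% and 4.3%, all above 2.5%.

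**Harm side.** 0 v 7: X² = 3.5 × 251/245 = 3.586, P=0.058. 0 v 8: X² = 4 × 251/244 = 4.115, P=0.0425. So harm needs 8 against none.

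**Error by direction.** Binomial(84, p) × Binomial(168, p) probabilities were summed over all tables with X² above 3.84, split by which arm has the higher rate.

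| Assumed risk p | Expected events, CM (84p) | Expected events, total (252p) | False benefit | False harm | Total |
|---|---|---|---|---|---|
| 0.5% | 0.42 | 1.26 | 2.9% | 0.0% | 2.9% |
| 1% | 0.84 | 2.52 | 4.2% | 0.01% | 4.2% |
| 2% | 1.68 | 5.04 | 3.4% | 0.4% | 3.8% |
| 3% | 2.52 | 7.56 | 3.0% | 1.1% | 4.1% |
| 5% | 4.20 | 12.60 | 2.7% | 1.8% | 4.5% |

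**After drop-out.** With 84 × 0.75 = 63 and 168 × 0.75 = 126 patients, the thresholds are the same: 2 v 0 gives P=0.0449, 0 v 7 gives P=0.057, 0 v 8 gives P=0.0415.

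**With an exact test (84 v 168).**

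| Events, CM v HBPT | Fisher P | Twice the smaller tail |
|---|---|---|
| 2 v 0 | 0.110 | 0.220 |
| 3 v 0 | 0.036 | 0.072 |
| 4 v 0 | 0.012 | 0.024 |
| 0 v 8 | 0.055 | 2 × 0.0369 = 0.074 |
| 0 v 9 | 0.032 | 2 × 0.0242 = 0.048 |

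Under the doubled-tail test, false benefit falls from 4.2% to 0.25% at 1% risk and from 3.4% to 0.8% at 2%. Power to detect harm also falls: from 31% to 23% at 1% v 5%, and from 6.0% to 3.0% at 1% v 3%.

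**The case against.** The strongest reply is that a condensed article names a default test, and that an exact fallback and the continuity correction are details for the statistical analysis plan. This carries some weight. With a continuity correction, 2 v 0 gives P=0.21 and the signal disappears, and a version stratified by the 12 centres could also differ. But the article does more than stay silent: it assigns this test to all categorical secondary endpoints at one threshold, with no exception. Read as written, that rule can produce the misleading claim.

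A second reply is that the plan promises a two-tailed level of 0.05, not 2.5% per direction, and that this level holds. That is correct. A reader might infer from the lopsided split that the overall false-positive rate is inflated. It is not: the total was at most 4.5% at the risks examined, up to 5%.

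A reader might also infer that nearly all rejections favour HBPT whatever the event rate, or that an excess under HBPT could hardly be flagged. Neither is supported. The split is 3.0% v 1.1% at 3% risk and 2.7% v 1.8% at 5%. Power for harm is 31% at 1% v 5% and 26% at 2% v 6%: low, but not near zero. The documents do not say that events will be rare; Study sites and population describes patients at raised short-term risk.

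Finally, much of the asymmetry belongs to the 1:2 allocation and would remain under an exact test (3 or 4 v 0 for benefit, 9 v 0 for harm). That stands, and it limits what the fix can achieve.

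**Conclusion.** The concern holds as a minor point on one kind of secondary endpoint. Applied as stated, the chi-square declares 2/84 v 0/168 a significant benefit when the exact P is 0.110. At an assumed equal risk of 0.5% to 3%, false benefit is 2.9% to 4.2% against a nominal 2.5% per side, and false harm is 0% to 1.1%.

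This rests on three assumptions that the protocol does not settle: few events, the uncorrected and unstratified form of the test, and item 12 analysed as patients with an event per arm. It does not show two-sided inflation and has no bearing on the primary endpoint or the sample size.

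**What to change.** Add one sentence to Planned statistical analyses. For cardiovascular events, and for any binary endpoint with an expected count below 5 in either arm, use an exact test in place of the chi-square, and report the number of patients with an event per arm with an exact 95% confidence interval for the difference in rates. Label the cardiovascular-event comparison descriptive.

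Name the exact test in advance. Fisher's removes the 2 v 0 signal but still calls 3 v 0 significant; twice the smaller tail removes both.

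No change to design, data or sample size is needed. The cost is conservatism: flagging harm takes 9 v 0 instead of 8 v 0. The low ability to detect harm remains, since it comes largely from the allocation and the few events. The interval and the descriptive label guard against reading a non-significant result as evidence of safety.
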